### Study development

#### Logistic phase

This phase will last 4 months and will include the following activities:

1. Training of the personnel that will participate in the study.

2. Acquisition of the materials required for the development of the project.

3. Elaboration of flyers, promotional and educative material, procedures manual and case report forms (CRFs).

4. Treatment randomization.

The treatment randomization will be realized by the epidemiologist of the Cardiovascular Foundation of Colombia. This randomization will be done in blocks in order to keep the size of the treatment groups similar, to avoid long sequences of the same treatment and to balance when possible some of the bias inherent to the simple randomization process. Additionally, this randomization in blocks will facilitate the execution of interim analyses.

#### Recruitment phase

This phase will take 22 months. In the selected municipalities, the health personnel that work in hospitals and health centers will receive training regarding the disease and the study methodology. Simultaneously an epidemiological focus study will be done with the leaders of the community and the health personnel to identify the geographic and demographic conditions with the purpose of developing strategies for the recruitment of possible cases of leishmaniasis. Subsequently, the subjects that present active ulcers with more than 2 weeks of evolution, with or without parasitological confirmation of CL, will be invited by the health promoters to attend the screening visit (Table 1).

**Table 1 T1:** Schedule of activities

**PROTOCOL ACTIVITIES**	**Screening Visit**	**Initial Visit**	**Treatment visits**	**Follow-up visits**			
				**Visit 1**	**Visit 2**	**Visit 3**	**Visit 4**
**SCHEDULE OF VISITS**		0	1–20	21+3	45 ± 7	90 ± 14	180 ± 14
Clinical History	X	X		X	X	X	X
Physical Examination	X	X		X	X	X	X
Inclusion/Exclusion criteria	X						
Informed Consent	X						
Direct test	X						
Sampling of cultures		X					
Laboratory tests		X		X			
Randomization		X					
Treatment administration		X	X				
Clinical assessment of the lesion	X	X	X	X	X	X	X
Measurement of ulcers		X		X	X	X	X
Photographic registration		X		X	X	X	X
Education of patients	X	X	X	X	X	X	X
Handing over of diary		X					
Evaluation of effectiveness				X	X	X	X
Documentation of adverse events	X	X	X	X	X	X	X
Recording of concomitant medications	X	X	X	X	X	X	X

### Screening visit

During this visit a complete clinical history will be elaborated and data about antecedents of leishmaniasis obtained (administered treatment, localization, number of lesions, etc). A full medical evaluation will be realized based on universally accepted techniques. The inclusion/exclusion criteria will be applied and the selected candidates informed about the study after which they will sign an informed consent. For those subjects with ulcers of more than two weeks of evolution without parasitological diagnosis a direct test will be performed by the parasitologist. If the first direct test is negative, it will be repeated up to three times; after which, in case of negative results, a biopsy will be performed. In case leishmaniasis is not confirmed the patient will be remitted to the original health center.

### Initial visit

The included patients will be randomly assigned in one of two groups. A culture in Novy-Nicolle-McNeal (NNN) medium will be taken for strain identification and a blood sample withdrawn from the antecubital vein for hepatic enzymes, creatinine, and pancreatic amylase determination. During this visit, a complete medical evaluation will be performed, the ulcer will be measured and a picture will be taken. Before taking the picture, a graduated rule will be placed next to the ulcer along with a sticker marked with the identification code of the participant, and the date of the visit. The first NOP (active or placebo) will be applied covering the lesion and the first shot of meglumine antimoniate (active or placebo) administered. The patients will receive information on how not to damage the patches and how to identify and report adverse events. To help the patients to do so, they will receive a diary to register them. The two groups randomly composed will be divided as follows:

Group 1: During 20 days this group will receive simultaneously intramuscular (IM) meglumine antimoniate (Glucantime^® ^20 mg/kg/day with a maximum dose of 3 ampoules per day); and an NOP placebo.

Group 2: During 20 days this group will receive simultaneously placebo of IM meglumine antimoniate (5–15 cc/day) and an active NOP.

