**Methods and design:**

A double-blind, randomized, double-masked, placebo-controlled clinical trial, including 620 patients from endemic areas for Leishmaniasis in Colombia was designed to investigate whether this patch is as effective as meglumine antimoniate for the treatment of cutaneous leishmaniasis but with less adverse events. Subjects with ulcers characteristic of cutaneous leishmaniasis will be medically evaluated and laboratory tests and parasitological confirmation performed. After checking the inclusion/exclusion criteria, the patients will be randomly assigned to one of two groups. During 20 days Group 1 will receive simultaneously meglumine antimoniate and placebo of nitric oxide patches while Group 2 will receive placebo of meglumine antimoniate and active nitric oxide patches. During the treatment visits, the medications will be daily administered and the presence of adverse events assessed. During the follow-up, the research group will visit the patients at days 21, 45, 90 and 180. The healing process of the ulcer, the health of the participants, recidivisms and/or reinfection will also be assessed. The evolution of the ulcers will be photographically registered. In case that the effectiveness of the patches is demonstrated, a novel and safe therapeutic alternative for one of the most important public health problems in many countries will be available to patients.

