### Treatment visits

The patients will visit the health center daily during 20 days to receive both the NOP (placebo or active) and meglumine antimoniate (placebo or active). Daily, the subjects and their adherence to the treatment will be assessed and the data collected. If any adverse event is detected, the patient will be referred immediately to the medical staff that will make an evaluation and report it to the adverse event committee that will take the final decision in each case.

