### Follow-up visits

This phase will last 10 months. During the follow-up, the patients will be seen by the research group in 4 opportunities. The first visit will take place the day after the end of the treatment (day 21) in which new blood samples will be taken for biochemical determinations. The second, third and fourth visits will be realized on day 45, 90 and 180 respectively. During these visits the healing process of the ulcer, the presence of recidivisms and/or reinfection and the health of the participants will be assessed. The evolution of the ulcers will be photographically registered.

The maximum and minimum diameters of the ulcer will be measured using a graduated ruler, and the induration using the ballpoint pen technique. The ulcer and induration areas will be calculated separately, and then registered in the CRF. The evaluation of the clinical response will be based on the ulcer showing the least improvement.

1. Complete clinical response: Complete reepithelization of the ulcer and disappearance of the induration.

2. Clinical Improvement: Reduction of more than 50% of the ulcer and the induration areas in relation to the last clinical evaluation.

3. Absence of clinical response: Increase or reduction of less than 50% of the ulcer and the induration areas in relation to the last clinical evaluation.

4. Therapeutic failure:

a. Increase in the size of the ulcer by more than 50% in relation to the last clinical evaluation

b. Presence of the ulcer three months after the beginning of the treatment.

c. Reactivation: Appearance of a lesion on the edge or in the center of the scar, with positive parasitological diagnosis, after a period of complete reepithelization.

d. Affection of the mucous membranes: Presence of affections of the mucous membranes during the treatment, at the end of it or in the follow-up visits.

5. Reinfection: Activation of an ulcer in an area different from the original lesion.

For subjects whose treatment will have been considered a failure the code will be broken and they will be remitted to their original health center to look for other therapeutic approach.

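### Table 1 marks dosing on day 0 and on days 1–20, which is 21 daily administrations against a stated course of 20 days

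*Protocol article*

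**What the plan says.** The course length is stated as 20 days in four places:

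- Abstract, Methods and design: "During 20 days Group 1 will receive simultaneously meglumine antimoniate and placebo of nitric oxide patches", with the matching regimen for Group 2.
- Initial visit, Group 1: "During 20 days this group will receive simultaneously intramuscular (IM) meglumine antimoniate".
- Initial visit, Group 2: "During 20 days this group will receive simultaneously placebo of IM meglumine antimoniate".
- Treatment visits: "The patients will visit the health center daily during 20 days to receive both the NOP (placebo or active) and meglumine antimoniate".

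The first dose belongs to the initial visit: "The first NOP (active or placebo) will be applied covering the lesion and the first shot of meglumine antimoniate (active or placebo) administered". The end of dosing is fixed by the Follow-up visits section, which places the first follow-up visit on "the day after the end of the treatment (day 21").

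Table 1, printed under Recruitment phase, puts day numbers on these visits. Its row "SCHEDULE OF VISITS" gives 0 for the initial visit, 1–20 for the treatment visits and 21+3 for the first follow-up visit. Its row "Treatment administration" has a mark under the initial visit and another under the treatment visits.

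**The concern.** A day 0 followed by days 1–20 covers 21 days. That is harmless if day 0 is a baseline day without a dose, or if dosing stops on day 19. Here neither applies: day 0 carries a dose and dosing runs through day 20, so the printed schedule and the stated course length cannot both be right.

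At stake is the number of doses given, not the inference. Staff who work from the table would give one more dosing day than the regimen calls for, and in Group 1 that is one more active injection of a drug for which the Background lists cardiac, hepatic and pancreatic effects. The count of doses due, against which the daily adherence assessment is made, becomes either 20 or 21, and so does the drug supply per patient.

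**Working it through.** **Inputs**

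- Stated course: 20 days (abstract; Initial visit; Treatment visits).
- Day labels: initial visit 0, treatment visits 1–20, first follow-up visit 21+3 (Table 1).
- Dosing marked at the initial visit and at the treatment visits (Table 1); first patch and first injection given at the initial visit (Initial visit).
- Day 21 is the day after treatment ends (Follow-up visits).
- Antimony dose 20 mg/kg/day, at most 3 ampoules per day (Initial visit).
- 310 patients per group (Sample size).

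**Step 1: can the stated 20 be reproduced from Table 1?** Day 0 contributes 1 administration and days 1–20 contribute 20. The total is 1 + 20 = 21, so it cannot.

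**Step 2: which numbering fits the text?** Let the first dose fall on day d, with n daily doses. The last dose is on day d + n − 1, and the day after treatment is day d + n, which must equal 21.

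- With n = 20: d = 21 − 20 = 1. The initial visit has to be day 1.
- With d = 0, as Table 1 has it: n = 21 − 0 = 21 doses.

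**Step 3: what has to give for the count to be 20?**

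| Dosing days | Doses | Statement contradicted |
|---|---|---|
| 0–20 (Table 1 as printed) | 21 | The 20-day course |
| 0–19 | 20 | Table 1's label 1–20, and day 21 as the day after treatment |
| 1–20, initial visit kept as day 0 without a dose | 20 | The first dose at the initial visit |
| 1–20, initial visit relabelled day 1 | 20 | Only Table 1's day labels |

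The last row leaves every statement in the prose intact, provided the 20 days in the Treatment visits section include the initial visit. If that section meant 20 further daily visits after the initial one, the prose would also lead to 1 + 20 = 21 doses and would contradict the 20-day regimen in the Initial visit section. The mismatch is present on either reading.

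**Step 4: size**

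- Dosing days: 21/20 = 1.05, or +5%.
- Group 1 cumulative antimony before the cap: 20 × 21 = 420 mg/kg against 20 × 20 = 400 mg/kg.
- Group 1 patient at the cap: 3 × 21 = 63 ampoules against 3 × 20 = 60.
- Whole trial, if every patient is recruited, completes the course and is dosed as the table reads: at most 310 × 1 = 310 extra active antimony doses in Group 1 and 310 × 1 = 310 extra active-patch days in Group 2.

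**The case against.** The best defence is that the regimen is clear from the text. Twenty days is stated repeatedly, no sentence prescribes 21 doses, and the table lists activities by type of visit and is not a dose count. On that view, 0 marks baseline and randomization, the initial visit falls on the same calendar day as treatment day 1, and the mark under the initial visit only records that the first dose is given there. That reading gives 20 doses. The article also mentions a procedures manual and case report forms, which are not shown and may carry the site dosing instructions, so nothing proves that staff would dose from the table.

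Part of this stands. The intended course is almost certainly 20 days, and the extra doses are what follows from a literal reading, so the totals are upper bounds. It is also true that the first-dose sentence is correct on its own; the fault lies in the table's labels.

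The same-day reading, however, is stated nowhere, and Table 1 gives the two visits separate columns and separate day numbers. If they were meant to coincide, the label 0 is wrong, which is the same finding. Condensation in a journal article does not explain it either: nothing has been left out, and the article prints a day-numbered schedule that disagrees with its own course length.

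**Conclusion.** The point holds and is minor. As printed, Table 1 together with the Initial visit and Follow-up visits sections schedules 21 daily administrations against a stated 20, an excess of one day per patient (+5%). The error is best placed in the table's day numbering, because starting on day 1 is the only choice that keeps the 20-day course, the first dose at the initial visit and the day-21 visit together. That attribution assumes that the 20 days of daily visits include the initial visit; the inconsistency itself does not depend on it. The figures for extra exposure assume that the table is followed literally.

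Both groups gain one day, so the schedule introduces no imbalance in the number of dosing days. The sample size, the endpoint and the between-group comparison are unaffected.

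**What to change.** In Table 1, label the initial visit day 1 and the remaining treatment visits days 2–20. Dosing then runs for 20 administrations, the last on day 20, with the first follow-up visit on day 21 as the text already says. A short table note that the initial visit is the first of the 20 treatment days would remove any remaining doubt, and the procedures manual and case report forms should be checked for the same numbering.

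The alternative of dosing on days 0–19 also gives 20 doses, but it would move the first follow-up visit to day 20 and require changes to both the table and the Follow-up visits section.

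The cost is two column labels. Measured from the first dose, the visits on days 45, 90 and 180 move by one day, well inside their windows of ±7, ±14 and ±14 days. Nothing in the design or analysis changes.

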### Treatment visits

The patients will visit the health center daily during 20 days to receive both the NOP (placebo or active) and meglumine antimoniate (placebo or active). Daily, the subjects and their adherence to the treatment will be assessed and the data collected. If any adverse event is detected, the patient will be referred immediately to the medical staff that will make an evaluation and report it to the adverse event committee that will take the final decision in each case.

### Follow-up visits

This phase will last 10 months. During the follow-up, the patients will be seen by the research group in 4 opportunities. The first visit will take place the day after the end of the treatment (day 21) in which new blood samples will be taken for biochemical determinations. The second, third and fourth visits will be realized on day 45, 90 and 180 respectively. During these visits the healing process of the ulcer, the presence of recidivisms and/or reinfection and the health of the participants will be assessed. The evolution of the ulcers will be photographically registered.

The maximum and minimum diameters of the ulcer will be measured using a graduated ruler, and the induration using the ballpoint pen technique. The ulcer and induration areas will be calculated separately, and then registered in the CRF. The evaluation of the clinical response will be based on the ulcer showing the least improvement.

1. Complete clinical response: Complete reepithelization of the ulcer and disappearance of the induration.

2. Clinical Improvement: Reduction of more than 50% of the ulcer and the induration areas in relation to the last clinical evaluation.

3. Absence of clinical response: Increase or reduction of less than 50% of the ulcer and the induration areas in relation to the last clinical evaluation.

4. Therapeutic failure:

a. Increase in the size of the ulcer by more than 50% in relation to the last clinical evaluation

b. Presence of the ulcer three months after the beginning of the treatment.

c. Reactivation: Appearance of a lesion on the edge or in the center of the scar, with positive parasitological diagnosis, after a period of complete reepithelization.

d. Affection of the mucous membranes: Presence of affections of the mucous membranes during the treatment, at the end of it or in the follow-up visits.

5. Reinfection: Activation of an ulcer in an area different from the original lesion.

For subjects whose treatment will have been considered a failure the code will be broken and they will be remitted to their original health center to look for other therapeutic approach.

### Procedures

#### Physical examination

A complete physical examination will be realized and vital signs will be measured.

### Blood samples withdrawn

Blood samples will be withdrawn from the antecubital vein to perform the following biochemical analyses:

1. Creatinine by spectrophotometry

2. Alanine transaminase (ALT) by spectrophotometry

3. Aspartate transaminase (AST) by spectrophotometry

4. Pancreatic amylase by spectrophotometry

### Sampling technique for the direct test of CL

A direct test is performed to confirm the presence of cells with amastigotes in a dermis scrape [46,47]; the sample must be, in so far as it is possible, free of blood, cellular detritus or pus. If the patients present several lesions, the sample must be taken from the one with the shortest time of evolution, the biggest induration area and/or the least purulent discharge. If the lesion has a scab it must be removed to improve the quality of the sample. The sample can be taken from the active edge or from the bottom of the ulcer. When the sample is taken from the active edge asepsis must be realized with alcohol at 70% and hemostasis then performed using the first and second fingers to make sure that there is no blood in the sample. A small incision of about 3 mm in length and depth is made with a scalpel in the active edge parallel to the edge of the ulcer. With the sharp side of the scalpel, a scrape is done in the dermic wall of the incision to obtain tissue. The extracted material is extended on two microscope slides. The sample is dried at room temperature, and then fixed with methanol and stained with Giemsa, Wright or Field. Using immersion oil the sample is observed under a microscope with a 100× lens, the presence of amastigotes of *Leishmania *assessed and their structure verified (nucleus, kinetoplast and cell membrane). If the sample is taken from the center of the lesion the same hemostatic technique must be used, the scab removed, and the bottom of the ulcer well cleaned using the sharp side of the scalpel to prevent the presence of cellular detritus and/or purulent material. This procedure must be continued until the granulomas are seen at the bottom. With the same technique used to process the samples from the active edge the presence of amastigotes of *Leishmania *is verified.

### Technique for the sampling of cultures

The sample for the culture may be obtained by suctioning the ulcer active edge or by extracting a fragment of tissue which is then macerated in a phosphate-buffered saline solution (PBS) with antibiotics (1000 UI of crystalline penicillin per cc), before it is put in the culture medium. A tuberculin syringe with a thin needle (26G), containing 0.3 cc of PBS solution with antibiotics is used in the suction technique. Previous asepsis of the ulcer with alcohol at 70%, a needle is introduced into the dermis and through rotating movements a small amount of tissue is macerated by the needle bevel during about a minute, after which it is suctioned into the syringe. The sample is deposited in aseptic conditions into a NNN culture medium and incubated at 26°C during 4 weeks [48,49]. Every week a drop is extracted from the culture medium and placed between two slides to be observed under a microscope. In case that promastigotes are not found, the cultures are rejected as negative [46]. The strains are identified by species using the monoclonal antibodies developed by [name] Mc Mahon Pratt [50, 51]

### Evaluation and management of adverse events

During the treatment and the follow-up visits, the patients will be asked about adverse events. Each adverse event will be classified by the physician as serious or non-serious(Table 2 and Table 3). A serious adverse event should meet one or more of the following criteria:

**Table 2 T2:** Toxicity grading scale for determining the severity of clinical adverse events

**SYSTEMIC**				
	**Grade 1 (Mild)**	**Grade 2 (Moderate)**	**Grade 3* (Severe)**	**Grade 4* (Life-threatening)**
Fever: oral^1^	38 – 38.5°C	38.6 – 39.5°C	39.6 – 40.5°C	>40.5°C
Headache^1^	Mild; no Rx required	Transient, moderate; Rx required	Severe; responds to initial narcotic Rx	Intractable; required repeated narcotic Rx
Allergic reaction^1^	Pruritus without rash	Localized urticaria	Generalized urticaria; angioedema	Anaphylaxis

**GASTROINTESTINAL**				

Nausea^1^	Mild discomfort; maintains reasonable intake	Moderate discomfort; intake decreased significantly; some activity limited	Severe discomfort; no significant intake; activities limited	Minimal fluid intake
Vomiting^2^	1 episode in 24 hours	2 – 5 episodes in 24 hours	> 6 episodes in 24 hours or needing IV fluids	Physiologic consequences requiring hospitalization or parenteral nutrition
Diarrhea^2^	Mild or transient; 3–4 loose stools/day or mild diarrhea lasting < 1 week	Moderate or persistent; 5–7 loose stools/day or diarrhea lasting > 1 week.	>7 loose stools/day or bloody diarrhea; or orthostatic hypotension or electrolyte imbalance or >2 LIV fluids required	Hypotensive shock or physiologic consequences requiring hospitalization
Oral discomfort^2^	Mild discomfort; no difficulty swallowing	Some limits on eating/drinking	Eating/talking very limited; unable to swallow solid food	Unable to drink fluids; requires IV fluids

